## 3. Treatment Monitoring

The study will be overseen by a Management and Safety Committee (MSC) and a Trial Management Group (TMG). The MSC is an independent committee and will meet quarterly to monitor participant recruitment, safety aspects, and implementation process. Reporting to the MSC, the TMG will meet fortnightly and will focus on day-to-day management of the study. An adverse event form will record the type, severity, start and end dates of each event, likely association to BUP/NX-F, and actions taken and outcome. Response to adverse events will follow the study protocol (Table S.1.). Implementation of the study procedures, data collection and management, and functions of the governance committees will be audited every 6 months. A random 5% audit of the material recorded during the medication management sessions will also be conducted with additional training provided as required.

## 4. Recruitment and Study Status

STAR-T is an ongoing study that commenced recruiting participants on 15^th^ of September 2014 and data analyses is still in progress.

## 5. Discussion

This pragmatic study will provide empirical data on the outcomes of personalising OAT in reducing opioid use and enhancing treatment retention. Personalised care was assumed by adjusting BUP/NX-F “take-home” prescriptions according to medication adherence, judged by TDM data, and drug use judged by UDS. This approach was hypothesised to optimise adherence and minimise diversion. This study evaluates the integration of TDM to provide stepped BUP/NX-F “take-home” against usual treatment. Findings from this study would contribute to the expanding OAT currently limited by poor compliance, concerns over diversion, and high cost supervised treatment [12] associated with high treatment dropout rates [6].

A practical alternative to prospectively assigning participants to BUP/NX-F dose schedules would be random assignment and stabilisation of participants followed by analysis of participant characteristics associated with each dose schedule. On the other hand, contrasting the level of medication adherence concluded by TDM with that generated by UDS would have strengthened the justification of using TDM considering the cost of both methods.

Although EQ-5D [58] is the approved tool for health utility calculations by the National Institute for Clinical Excellence (NICE) in the UK, EQ-5D does not offer the required sensitivity to assess mental health disorders of nonacute presentations. This has encouraged the authors to explore WSAS as a brief and self-administered measure of disability and inversely utility to estimate changes in quality of life (QOL). For future research we suggest the validation of WSAS against a standard tool measure of QOL like Short Form Health Survey-Arabic version (SF-36, [59])

Blood is the biological matrix identified by the TDM consensus guidelines for quantitation of BUP [24]. In blood, BUP demonstrates linear kinetics and time to peak concentration has been established [24, 60]. In contrast, detection of BUP in urine is performed but quantitation was not recommended due to erratic clearance with approximately 30% of BUP excreted in urine. Equally important, time to achieve BUP peak concentration was not established in urine unlike blood [60].

The identified strengths allowing for generalisability of results include expanded inclusion criteria and exclusion of factors reported to minimise retention, e.g., unstable housing arrangements [15]. The 16-week period could be optimal for evaluating relapse prevention. On the other hand, the extended turn-around time to report BUP levels might influence the effectiveness of CM based interventions shown to be most effective when provided within 24 hours of the behaviour [11]. Other possible limitations include applying nonstratified randomisation due to the extended stratification factors and blocks include city of residence; type and pattern of opioid use; polysubstance use; and comorbid anxiety, depression, and impulsiveness. Categorical reporting of retention limits assessing the potential value of partial completion. In the absence of consensus on defining treatment retention, we chose the most stringent definition of retention which is maintaining access to treatment at different treatment points including the end of the study [61].

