## 2. Methods

### 2.1. Study Design, Population, and Setting

The Suboxone Treatment and Recovery Trial (STAR-T) is a single centre, 16-week outpatient intervention, two-arm, pragmatic, phase IV randomised controlled trial of OAT and adjunctive TDM for OUD. The study population is adults (≥ 18 years) with current OUD.

The study setting is the specialist OUD treatment and care programme operated by National Rehabilitation Centre (NRC), Abu Dhabi, United Arab Emirates (UAE; www.nrc.ae). In the UAE, use and combination use of heroin, morphine, and illicit tramadol are the most prevalent [29, 30]. The NRC treatment programme includes an inpatient unit for assessment and management of medical and mental health comorbidities with (poly) substance and alcohol use disorders [29–31]. In 2002, the NRC introduced OAT with BUP with induction and stabilisation procedures conducted in the inpatient unit. However, following concerns about medication diversion in 2011, the NRC suspended all new admissions to OAT pending the development and findings from the present study.

Following a standard of care protocol for OAT, all participants will first complete inpatient care (up to four weeks) to achieve medically supervised withdrawal and stabilisation on BUP/NX-F and to estimate the BUP Elimination Rate (EL.R). After study enrolment and prior to discharge, participants will be randomly allocated (1:1: using an online randomisation service [32] with no stratification) to an experimental group (that immediately received 16 weeks of outpatient BUP/NX-F maintenance, standard case management, and manualised adjunctive medication management with TDM monitoring and CM) or to a treatment-as-usual, control group (that immediately received BUP/NX-F and standard case management and usual medication management only). Using ongoing medication management, TDM, and CM protocol, participants in the experimental group will be able to receive up to four weeks of medication on a take-home basis. All participants will continue to receive ongoing treatment after 16 weeks as usual.

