### 2.4. Research Assessments

The following measures were recorded prior to randomisation (baseline), during the outpatient treatment phase (as shown in parentheses; see Table 2 for summary)

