### 2.9. Statistical Analysis of the Primary and Secondary Outcomes

Data for the whole population and by study group will be analysed for mean, standard deviation, 95% confidence interval, and range. With no interim analysis, all statistical analyses will be pragmatically done according to intention-to-treat principle. All analyses will be conducted using two-sided 5% significance test. A fixed-effects logistic model will be applied to analyse the primary outcome. To analyse between group differences, student* t*-test will be conducted for normally distributed data, or a Mann-Whitney test. For the primary outcome, a planned sensitivity analysis will determine the impact of the imputed or complete case [57]. Alternatively, reported observed opioid screens or actual screens without imputation will be analysed between group differences. Secondary outcome will be evaluated using proportional hazards regression model and Chi-Square test will be performed to measure between group differences.

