### 2.10. Analyses for Exploratory Outcome

Bivariate correlation tests to explore correlations with study outcomes will be performed. Specifically, Pearson's correlation will be applied for continuous and Spearman's rho test for categorical data. Factors demonstrating significant correlation and those with potential impact on the primary outcome will be studied for predictive power using a simple linear regression model. Finally, analysing for the effect of confounders will be done using univariate analyses for factors generating higher correlation (>0.5). The mean change from baseline scales or within group change will be analysed using a generalised linear model framework. A paired* t*-test will be conducted where normal distribution is assumed or alternatively Kruskal-Wallis test. The magnitude of change from baseline will be estimated using bias corrected Hedge's* g* effect size. Mean difference between groups will be analysed using student* t*-test where normal distribution is assumed or a Mann-Whitney test.

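### The tests named for group differences ignore baseline values already collected, and covariates are to be picked by observed correlation, which wastes precision after unstratified randomisation

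*Protocol article*

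**What the plan says.** **Allocation.** Section 2.1 describes 1:1 allocation "using an online randomisation service [32] with no stratification". Section 5 gives this as a possible limitation: "applying nonstratified randomisation due to the extended stratification factors and blocks include city of residence; type and pattern of opioid use". That sentence goes on to polysubstance use and comorbid anxiety, depression and impulsiveness.

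**Primary and secondary outcomes (section 2.9).** Two kinds of analysis stand side by side.
- Primary: "A fixed-effects logistic model will be applied to analyse the primary outcome". The next sentence turns to group differences, for which a t-test "will be conducted for normally distributed data, or a Mann-Whitney test".
- Retention: "Secondary outcome will be evaluated using proportional hazards regression model and Chi-Square test will be performed to measure between group differences".
- No covariates are named for either model, and none are ruled out.

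**Psychosocial scales (section 2.10).** A generalised linear model framework is tied to change from baseline or change within a group. For the contrast between arms: "Mean difference between groups will be analysed using student" t-test, or Mann-Whitney.

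**Confounders (section 2.10).** "analysing for the effect of confounders will be done using univariate analyses for factors generating higher correlation (>0.5".

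**Baseline data.** Section 2.4 says: "The following measures were recorded prior to randomisation (baseline". Table 2 shows PHQ-9, GAD-7, BIS-11, PSQI and WSAS at baseline and again at week 16.

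**The concern.** When allocation is not stratified, the usual remedy is to adjust for a few baseline factors chosen beforehand. Here the trial holds those values. The Introduction cites depression and anxiety as predictors of discontinuation and heroin use, and impulsiveness as a predictor of noncompletion. Injecting status, opioid type and polysubstance use must be known to assign the dosing schedule (section 2.6.1). Yet the tests named for the arm contrast cannot take a covariate.

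The one step that looks at confounders chooses them from their observed correlation with outcome and handles them one at a time. The threshold is also high: a correlation of 0.5 means 25% of variance explained. A factor explaining 10-20% (correlation about 0.32-0.45) would be passed over although adjusting for it would help.

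At stake are the width of the confidence intervals and how far one unlucky allocation can move the estimate.

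**Working it through.** **1. Size of the trial.** Section 2.8 gives 92 without saying whether this is per group or in total, and states no control rate. Assume a control rate of 0.30. With OR 2.56 the other rate is 0.523, and the log-odds-ratio formula gives

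n = (1.96 + 0.842)² × [1/(0.30×0.70) + 1/(0.523×0.477)] / (ln 2.56)² ≈ 78 per arm.

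The 15% uplift gives 78/0.85 ≈ 92. So 92 fits as a per-arm figure. Read as a total, it gives power of at most about 54% (40 evaluable per arm) at control rates from 0.10 to 0.60. I use 92 per arm.

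**2. Chance imbalance in a binary factor of prevalence p.** 95% limit = 1.96 × √(2p(1−p)/92).

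| p | limit |
|---|---|
| 0.30 | 1.96 × √(0.42/92) = 13.2 points |
| 0.50 | 1.96 × √(0.50/92) = 14.4 points |

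The Introduction puts mental comorbidity at 40-55%. In that range, the chance of a gap of at least 10 points is about 17%, and of at least 15 points about 4%.

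**3. Continuous outcome, such as the percentage of negative UDS in the abstract.** Adjustment multiplies the SE by √(1−R²). The documents give no R², so it is assumed. Power is for 78 evaluable per arm and an effect that gives 80% unadjusted.

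| R² | SE ratio | SE reduction | Power |
|---|---|---|---|
| 0.10 | 0.949 | 5% | 84% |
| 0.20 | 0.894 | 11% | 88% |
| 0.30 | 0.837 | 16% | 92% |

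Simulation with 8,000 trials per scenario, at R² of 0.10 and 0.30, gave type I error of about 5% both with and without adjustment, and adjusted power of 84% and 91%. So the unadjusted test is valid, only less efficient.

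This formula does not carry over to the log odds ratio of the logistic model. There, adjustment does not shrink the SE in this way; the gain shows as power, and the odds ratio becomes conditional on the covariates.

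**4. Psychosocial scales.** Let r be the correlation between baseline and week-16 score (assumed), with equal variances at the two times. Variances relative to a t-test on week-16 scores are 1−r² for ANCOVA and 2(1−r) for a t-test on change.

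| r | ANCOVA | Change score | ANCOVA vs week-16 test | ANCOVA vs change test |
|---|---|---|---|---|
| 0.3 | 0.91 | 1.40 | 9% lower | 35% lower |
| 0.5 | 0.75 | 1.00 | 25% lower | 25% lower |

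**The case against.** A reader might infer that every between-group comparison is unadjusted. The text does not support that. Section 2.9 names a logistic and a proportional hazards model, and section 2.10 a generalised linear model framework. All of these can carry covariates, and the article is silent on them. A covariate list is commonly left to a statistical analysis plan, which is not shown. Silence about the models is therefore no finding. What remains is what the article does state: tests for group differences that cannot adjust, and a covariate rule driven by observed correlations.

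A reader might also infer that the missing stratification is a mistake, or that it biases the result. Neither holds. Treating the seven listed factors as binary gives 2⁷ = 128 strata, or 184/128 ≈ 1.4 participants each, which bears out the stated reason. Chance imbalance is already covered by the error rate of the unadjusted test.

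Nor do the documents show that the listed factors are strongly prognostic: no effect sizes are given, and impulsiveness is cited only for noncompletion. The R² range is my assumption.

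The scales are exploratory outcomes. Their baseline is taken at intake, before detoxification, so r may be modest, which is why a range is shown. Even at r = 0.3, ANCOVA is the more efficient choice.

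**Conclusion.** The point holds in a limited form. The named t-test, Mann-Whitney and chi-square comparisons leave unused the baseline information that the trial collects before randomisation, and choosing confounders by observed correlation is a poor substitute for a prespecified list. The cost is efficiency and exposure to chance imbalance, not bias or a wrong error rate.

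The imbalance limits rest on 92 per arm. The SE reduction of 5-16% rests on an assumed R² and a linear model of a continuous outcome. The gain for the scales rests on an assumed r. The case is clearest for the scales, where each measure has its own baseline. For the primary and retention outcomes, it is that the article should say which analysis is the group comparison and settle its covariates in advance. This is worth changing, but it does not threaten the validity of the trial.

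**What to change.** 1. **Scales.** Replace the between-group t-test or Mann-Whitney with ANCOVA of the week-16 score on arm and that scale's baseline.
2. **Primary and retention outcomes.** Name the logistic and proportional hazards models as the group comparison, with a short covariate list fixed without reference to outcome by arm. For example: opioid type or injecting status, polysubstance use, baseline PHQ-9 and baseline BIS-11. State that the adjusted odds ratio is conditional on these.
3. **Confounder rule.** Drop selection by observed correlation above 0.5 as the route to adjustment.
4. **Reporting.** Give the unadjusted result beside each adjusted one.

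This needs a change of wording only. The scale baselines are already collected, and opioid type, injecting status and polysubstance use are already needed to assign the dosing schedule. One caution: section 4 says that data analyses are in progress. The list should be dated, with a statement of whether outcome by arm had been seen. If it had, the adjusted results should be labelled as specified late.

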## Figures and Tables

**Figure 1 fig1:**
[figure not shown]
Dose assignment and stabilisation.

**Table 1 tab1:** Participant inclusion and exclusion criteria.

*Inclusion criteria*
For a participant to be enrolled into the study he must fulfil all the following inclusion criteria:
(1) Aged 18 and above with no upper limit (usually 64 years);
(2) Current diagnosis of OUD;
(3) Voluntarily seeking OAT treatment;
(3) Resident in the UAE;
(4) Evidence of stable accommodation.

*Exclusion criteria*
Otherwise eligible patients will be excluded from the study for any of the following:
(1) Benzodiazepine use in excess of 20 mg daily diazepam equivalent in the past 28 days;
(2) Known naloxone or BUP hypersensitivity;
(3) Pregnancy;
(4) Hepatic impairment (elevation of liver function tests three times normal);
(5) Suicide attempt in past 12 months;
(6) Involvement in criminal justice system which is likely to result in arrest and incarceration;
(7) Uncontrolled severe mental or physical illness judged to compromise safety;
(8) Mini Mental State Examination score < 17 indicating cognitive dysfunction.

**Table 2 tab2:** Schedule for administering study measures.

Tool/ Screen	Baseline Intake	Inpatient		16 week outpatient study period				
		Detoxification (Daily)	Stabilisation (Weekly)	Week 1 to 4	Week 5 to 8	Week 9 to 12	Week 13 to 16	Week 16 End of study
Eligibility Screen	x							

MCCS	x	x	x	x	x			

Pupil Reflexes	x	x	x	x	x		x	x

COWS	x	x	x	x				

PHQ-9	x			x		x		x

GAD-7	x			x		x		x

BIS-11	x			x				x

PSQI	x		x	x	x	x	x	x

WSAS	x			x				x

PDS	x			x				x

ASI-Lite	x			x				x

MCCS: Minnesota Cocaine Craving (adapted for opioids); PHQ-9: Patient Health Questionnaire; COWS: Clinical Opioid Withdrawal Scale; GAD-7: Generalised Anxiety Disorder; BIS-11: Barrett Impulsiveness Scale; WSAS: Work and Social Adjustability Scale; PDS: Personality Disorder Screen; ASI-Lite: Addiction Severity Index-Lite.

**Table 3 tab3:** Interventions under study groups (TDM; TAU).

Intervention	Randomisation Group	
	TDM	TAU
Induction	Yes	Yes

Stabilisation	Yes	Yes

Baseline assessments	Yes	Yes

Estimating BUP Elimination Rate	Yes	Yes

Medication education	Yes	Yes

Emergency card	Yes	Yes

*Outpatient DOT*	*Yes*	*No*

*Outpatient medication management manualised intervention*	*Yes*	*No*

UDS at outpatient care	Yes	Yes

Providing prescription take-home doses	Contingent on UDS & TDM (i.e., abstinence & adherence)	Contingent on UDS only

*Stepped BUP/NX-F take-home doses*	*Yes*	*No*

Maximum take BUP/NX-F home doses	*4 weeks*	*2 weeks*

*TDM *	*Yes*	*No*

Periodic study assessments	Yes	Yes

End of study assessments	Yes	Yes

Psychosocial support	Yes	Yes

BUP: buprenorphine; DOT: directly observed treatment; UDS: urinary drug screen; TDM: therapeutic drug monitoring.

## Data Availability

Data supporting the findings of this study are available from the NRC (www.nrc.ae) but restrictions apply to the availability of data used under license for the current study. Public availability of materials is not applicable due to concerns of violating patient confidentiality. However, data are available from the corresponding author upon reasonable request and permission of the NRC.
